#### Emergency measures

Adverse reactions known and associated with more intense dosing regimen proposed for Miltefosine are vomiting and diarrhea.

There must be an attentive observation and given the appropriate supportive treatment, adverse drug reactions suggested should be treated symptomatically.

##### Concomitant

All concomitant medications (including prophylactic medication, if any) and any treatments (prescribed and non-prescription) must be recorded in medical records, brand-name and generic name, route or formulation, dosing, indication and starting dates and end of the administration. Any changes that occur during the study should be documented, too.

To allow the symptomatic treatment of adverse effects and treatment of concomitant diseases not associated with cutaneous leishmaniasis, is decided by the investigator, is desirable.

#### Rescue treatment

Rescue treatment will be started if there is deterioration in clinical condition probably attributed to cutaneous leishmaniasis despite treatment of the study.

Rescue treatment for a patient who is not getting hit during or after the use of Miltefosine, will be the standard treatment, according to standard procedures of the institution of the researcher.

### **3.4 Evaluation of clinical response**

#### Effectiveness

The eradication of *Leishmania* led to clinical cure is the goal of treatment.

A definite cure requires the complete healing of skin ulcerations at the end of 6 months of follow-up period.

#### Methods

##### *Clinical evaluation, photographic documentation*

Each ulcer is measured by size (two dimensional diameter, larger in mm), and evaluated for their degree of epithelialization. A standardized photograph will be taken before, during (14 days) at the end of treatment (28 days) and after treatment (1, 2, 6 months).

##### *Parasitology*

For each lesion that is not completely epithelialized, there will be a parasitologic selection (diagnosis). Parasitological examination of additional lesions that are not fully cured will be held 2 weeks after the end of treatment and / or during follow-up. Tissue samples will be collected by one of the following methods: skin smear, aspirate, biopsy.

##### *Evidence of infection include:*

Microscopic identification of amastigotes of *leishmania* in Giemsa staining direct (smear) and / or the demonstration of mobile promastigotes cultured aspirate and / or a biopsy of the lesion and / or by PCR identification.

The presence of parasites (the inclusion or treatment failure) is sufficiently demonstrated by a positive finding with one of three methods (swab / aspirate / biopsy) in a lesion.

#### Response criteria (efficacy)

##### *Apparent cure*

Complete healing of all ulcers until 2 months after completion of treatment.

*Definitive cure*

Complete re-epithelialization with a characteristic scar and no inflammation of all ulcers at the end of 6 months of follow-up period.

*Partial healing*

Incomplete epithelialization of one or more lesions.

*Clinical failure*

Any of the following points will qualify for treatment failure: residual lesions with the presence of parasites, or development of any new lesion or > 50% increase of lesions previously documented 2 months after the end of treatment or at any time during the monitoring period.

If a patient meets the criteria of partial healing, two months after the end of treatment, the response will be evaluated as clinical failure and the patient will receive salvage treatment.

If no parasitological analysis is performed 2 months after the end of treatment / or during the monitoring, evaluation of clinical failure will be based only on clinical criteria. A positive parasitological result at or after the 2 months after the end of treatment, always define a treatment failure.

Provision of patient

Apparent cure or partial cure: The patient will be monitored (up to 6 months after the end of treatment). Every patient who is not clinically cured 2 months after the end of treatment will receive rescue treatment.

Clinical failure at any time after the end of treatment: rescue treatment with parenteral standard Sbv therapy.

Security - Adverse Events

*Definitions*

An adverse event (AE) is any untoward medical occurrence in a patient or individual participant in clinical research administered with a pharmaceutical product that does not necessarily have a causal relationship with this treatment. An adverse event (AE) can therefore be an unfavorable sign or unintentional including an abnormal laboratory finding (or vital, ECG, etc.), symptom or disease temporarily associated with the use of a drug under investigation, or related not this drug.

Serious adverse event (SAE) means any untoward medical occurrence that at any dose results in death, is a risk to the life, the patient requires hospitalization or prolongation of existing hospitalization, results in disability or significant disability or incapacity, is a congenital anomaly / inborn defect or other condition is a clinically important

A The term "life threatening" in the definition of "serious" refers to an event in which the patient is at risk of death at the time of the event, does not refer to an event that hypothetically might have caused the death would be more serious.

B clinically important conditions that may not result in death, be life-threatening or require hospitalization may be considered when SAE, based on appropriate clinical trial, may involve risk to the patient or require intervention to prevent one of the outcomes listed in the above definition .

Note: The term "severe" is often used to describe the intensity (severity) of an event (as in mild pain, moderate or severe), the event itself may be of relatively minor clinical significance (such as severe headache). Not the same as "serious", which is based on the outcome of event / patient or action criteria usually associated with events that pose a risk to the patient's life or vital function. Seriousness (not severity) serves as a guide for defining regulatory reporting obligations.

*Procedures in case of adverse events*

The investigator should ask the patient at each visit if he / she had any medical problem or not unusual.

All adverse events that occur during the study treatment should be documented, regardless of the assumption of a causal relationship in respective page of the report form (CRF). All symptoms / complaints that have occurred in the last 14 days before the first exposure to study treatment should be documented in "Complaints at Baseline" medical records.

The documentation of adverse events including start and end date, severity, according to the CTCAE criteria, and seriousness. The investigator should also assess the likelihood of a causal relation of adverse event to study medication as probable, not assessable, or unlikely. The information provided in the investigator's brochure can give support to this evaluation.

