### 3.2.3 Criteria for withdrawal

A premature withdrawal or discontinuance shall be construed as withdrawal procedures of the study after the first exposure to study treatment. Withdrawals before that time should be considered "failures of selection."

Patients may be withdrawn from the study at any time at its own request or on the basis of clinical trial investigator. However, patients who request the withdrawal will be strongly encouraged to conduct appropriate tests to make a valid assessment and possible inclusion in the analysis.

The reasons for withdrawal are classified as follows:

**Lack of effectiveness:** The patient showed inadequate response to treatment or deterioration.

**Lack of tolerance:** the dose-limiting intolerance reported by patients or observed by the doctor and found to be "probably" related to study treatment (and therefore does not refer to an aggravation of a preexisting condition).

An adverse event is considered dose limiting toxicity if he understands grade 3 or 4 of the common terminology criteria for adverse events (CTCAE) and is confirmed by a re-assessment within a week.

In the case of treatment of grade 3 transaminase elevation CTCAE, the investigator may decide to continue treatment until no manifestation of liver injury is observed (eg. Jaundice), additional control tests are designed to ensure patient safety.

The CTCAE grade 4 elevation of enzyme (s) impairment (s) or clinical signs of liver damage require immediate discontinuation of study treatment.

**Intercurrent disease:** A disease or condition that occurred or worsened during the study and prevented the completion of treatment and procedures of the study, however, no evidence of a causal relationship to study treatment, the adverse event record corresponding to classify causality as "unlikely" or "not assessable".

**Withdrawal of consent / non-adherence:** The patient, parent or legal guardian withdrew consent or the patient did not adhere to study procedures (must be verified if an adverse event caused withdrawal).

**Other (s) reason (s):** Reason for discontinuation not approached by any of the criteria above, p. ex., moving the patient, other reasons must be specified.

Patients who are withdrawn from the study will not be replaced.

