### **4.3 Assessments at the end of treatment**

The end of treatment will be the 28th day in the case of regular treatment. In case of premature discontinuation, all assessments listed below will be executed whenever the treatment is discontinued.

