#### 4.6 Flowchart

|                                                          | Visit | 1 a) | 2     | 3     | 4      | 5      | 6 b)         | 7                                | 8                                | 9                                 | 10                                | 11                                |
|----------------------------------------------------------|-------|-----------------|-------|-------|--------|--------|-------------------------|----------------------------------|----------------------------------|-----------------------------------|-----------------------------------|-----------------------------------|
| Evaluation                                               | Day   | Before therapy  | Day 1 | Day 7 | Day 14 | Day 21 | Day 28 or final therapy | 2 weeks after the end of therapy | 1 month after the end of therapy | 2 months after the end of therapy | 4 months after the end of therapy | 6 months after the end of therapy |
| Informed consent                                         |       | x               |       |       |        |        |                         |                                  |                                  |                                   |                                   |                                   |
| Medical history                                          |       | x               |       |       |        |        |                         |                                  |                                  |                                   |                                   |                                   |
| History leishmaniasis                                    |       | x               |       |       |        |        |                         |                                  |                                  |                                   |                                   |                                   |
| Parasitology (fecal / blood)                             |       | x               |       |       |        |        |                         |                                  |                                  |                                   |                                   |                                   |

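### Section 3.4 prescribes parenteral antimony as rescue for every clinical failure, in either arm, with no exception for a patient who did not tolerate antimony

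*Protocol*

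**What the plan says.** Three statements in section 3.4 (Response criteria) determine who is rescued and with what.

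- A patient with only partial healing 2 months after treatment is a failure: "the response will be evaluated as clinical failure and the patient will receive salvage treatment".
- Rescue at that time is universal: "Every patient who is not clinically cured 2 months after the end of treatment will receive rescue treatment".
- The drug is named: "Clinical failure at any time after the end of treatment: rescue treatment with parenteral standard" pentavalent antimony.

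A separate Rescue treatment paragraph in section 3.3.3 names the standard treatment, following the institution's own procedures, but only for a patient rescued during or after miltefosine.

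For patients who stop early, section 4.3 says: "The end of treatment will be the 28th day in the case of regular treatment". It continues: "In case of premature discontinuation, all assessments listed below will be executed whenever the treatment is discontinued". The flowchart in section 4.6 labels that visit "Day 28 or final therapy" and times the key follow-up visit as "2 months after the end of therapy". Section 3.2.3 points the other way: "A premature withdrawal or discontinuance shall be construed as withdrawal procedures of the study after the first exposure to study treatment".

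Section 5.2 acknowledges serious antimony toxicity, listing pancreatitis and arrhythmias. It also describes amphotericin B as the second-choice drug, but nowhere makes it the trial's rescue.

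**The concern.** In the control arm the rescue drug is also the study drug. Section 3.2.3 foresees stopping study treatment for intolerance, and demands an immediate stop for grade 4 enzyme elevation or clinical signs of liver damage. For a control patient the drug stopped is antimony. If that patient is still unhealed 2 months later, the rescue sentence prescribes antimony again. The protocol recognizes the hazard in one section, while its rescue rule in another makes no allowance for it.

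What is at stake is the safety of a few patients. A written rule that conflicts with sensible care also puts the investigator in an awkward position at the moment of decision.

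**Working it through.** The protocol gives no figure to reproduce, so the check is mainly a reading of the sections side by side.

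**1. Is there an exception or an alternative drug anywhere?**

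| Section | What it offers a control patient intolerant of antimony |
|---|---|
| 3.2.2 Exclusion criteria | Screens for serious organ disease, abnormal liver and renal tests, and pregnancy, at entry only |
| 3.2.3 Withdrawal | Foresees stopping for intolerance; names no onward treatment |
| 3.3.3 Modifications | Deals with patients who do not tolerate miltefosine |
| 3.3.3 Concomitant | Allows symptomatic treatment of adverse effects; no rescue drug |
| 3.3.3 Rescue treatment | Institutional procedures, for miltefosine patients only |
| 3.4 Provision of patient | Antimony, without exception |
| 5.2 Risk-benefit | Mentions a second-choice drug, but not as trial rescue |

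None of these supplies an exception.

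**2. Could the rescue sentence be meant for the miltefosine arm alone?** The text does not say so. If it were, control failures would still have to receive rescue, because the 2-month rule covers every patient, and no drug would be named for them. The sentence needs amending on either reading.

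**3. Does the rule reach a patient who stopped early?** Section 4.3 ties day 28 to regular treatment and moves the end-of-treatment assessments to the point of stopping. The flowchart counts later visits from the end of therapy, whenever that falls. Together these suggest that the patient continues to the 2-month assessment under section 3.4. Section 3.2.3 construes discontinuation as withdrawal, which could take the patient out. The first reading is the more natural one, but it is not certain.

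**4. How many patients?** Section 3.2 plans 90 patients, 60 on miltefosine, so controls number 90 − 60 = 30. That is a ceiling. The protocol gives no rate for the joint event (antimony toxicity that should bar re-exposure, and unhealed at 2 months). Purely as an illustration, for an assumed share *p* of controls the expected number is 30*p* and the chance of at least one such patient is 1 − (1 − *p*)^30:

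| Assumed *p* | Expected patients | Chance of at least one |
|---|---|---|
| 0.1% | 0.03 | 3% |
| 1% | 0.3 | 26% |
| 3% | 0.9 | 60% |
| 5% | 1.5 | 79% |

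The spread shows that the answer depends almost wholly on the assumption.

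**5. Does the primary endpoint move?** Under section 3.4 a patient is classified as a failure first and rescued afterwards. The choice of rescue drug therefore does not alter the response already assigned.

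**The case against.** The strongest reply is that the patient in question has left the trial. Lack of tolerance is a listed reason for withdrawal, and section 3.2.3 treats discontinuation as withdrawal, so section 3.4 may no longer govern care. The investigator may also withdraw any patient on clinical judgement, and section 5.1 commits the trial to good clinical practice and the Declaration of Helsinki. This stands in part. Re-exposure is not the certain effect of the text, and an investigator can protect the patient without breaching the protocol. It does not remove the gap: sections 4.3 and 4.6 favour the reading that keeps the patient in, and withdrawing someone to avoid a rescue rule is a poor substitute for a correct rule.

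A second reply concerns contraindications. Any randomized patient could have been allocated to antimony, and section 3.2.2 removes most contraindications at entry. That stands; only those arising on study remain. Miltefosine patients also have the latitude of section 3.3.3.

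Three stronger readings are tempting, and the documents do not support them:

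- **Many miltefosine patients are put at risk.** Applying the cure rates of 33% to 82% in section 1 to 60 patients gives 60 × 0.67 ≈ 40 down to 60 × 0.18 ≈ 11 failures sent to antimony. But these patients would be receiving the intended first-line drug without having had it before. The count says nothing about harm.
- **A re-exposed patient is likely.** The larger percentages in the table rest on an assumed rate with no source in the protocol.
- **The efficacy result is compromised because early stoppers have no defined response.** How they are classified and analysed is commonly left to the statistical analysis plan, which is not at hand. It is no finding here.

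**Conclusion.** The point holds as a limited patient safety matter. The rescue sentence in section 3.4 is unconditional, no other section qualifies it for control patients, and, if an antimony-intolerant control remains under section 3.4, the rule as written re-exposes that patient to the same drug. It rests on one assumption about the text, that early stoppers stay under section 3.4, which is the likelier reading but is left unclear by section 3.2.3.

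The size is an unknown and probably small number among at most 30 controls, plus any patient in either arm whose contraindication arose on study. Sample size, error rates and the primary endpoint are unaffected. The change is a useful clarification that the sponsor could make; the trial does not depend on it.

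**What to change.** Amend the rescue sentence in section 3.4 along these lines: rescue is parenteral pentavalent antimony unless, in the investigator's judgement, the patient had clinically significant antimony toxicity or now has a contraindication to antimony; in that case an alternative is used, such as the second-choice drug in section 5.2. This applies also to patients who stopped treatment early.

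The exception should rest on judgement, not on the dose-limiting toxicity definition in section 3.2.3. That definition needs grade 3 or 4 confirmed on re-assessment within a week, so an arrhythmia or pancreatitis that settled once antimony was stopped might not qualify, and the patient could still be sent back to the drug. In the other direction, section 3.2.3 lets the investigator continue treatment through a grade 3 transaminase rise, which a fixed grade threshold would turn into a bar.

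The cost is a sentence or two of protocol text, with no added patients or visits. The real downside falls on the few patients affected. They may need amphotericin B, which according to section 5.2 means hospital admission and higher cost and carries risks of drug fever and renal dysfunction. The investigator has to weigh that for each patient.

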## 2. OBJECTIVES

The objective of this trial is to assess if therapeutic activity and safety of oral miltefosine patients with CL caused by *L. braziliensis* in an endemic area of Bahia state is similar or superior to the standard treatment (meglumine antimoniate – Glucantime®).

Primary endpoint:

- Rate of final cures (6 month after treatment)

Secondary endpoints:

- Rate of initial cure (2 month after treatment)
- Incidence and severity of adverse events

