#### 3.3.3 Administration of study treatment

##### Miltefosine

The dose and dosing schedule will be as follows:

Via: Oral

Dose for Target dose of 2.5 mg / kg body weight per day;  
Group 1: daily dose rounded to the next increment of 10 mg;  
Patients over 20 kg will receive 1 capsule of 50 mg per day

Dose for Patients > 25 kg body weight: 100 mg / day, or one capsule of 50 mg in the morning and one  
Group 2: capsule of 50 mg at night and after meals

Patients <25 weight: 50 mg / day, ie a capsule of 50 mg in the morning after meal

Duration: The duration of study treatment is 28 days

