### **4.2 Assessments during the study**

#### **Safety assessments:**

|                         |              |
|-------------------------|--------------|
| Vital parameters        | 7, 14, 21    |
| Adverse Events          | continuously |
| Laboratory              |              |
| - CBC                   | 7, 14, 21    |
| - Clinical Biochemistry | 7, 14, 21    |

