#### 4.4 Assessments 2 weeks, 1 month and 2 months after the end of the treatment

**Efficacy variables:** Lesion size / epithelization grade / size of the infiltration in the lesion  
Photograph of each lesion  
Leishmania parasitology  
Response to study treatment

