### **5.2 Consideration of risk-benefit**

Cutaneous leishmaniasis is a disease that is associated with clinically relevant morbidity, especially if the infection is widespread, diffuse or involve children (20% of cases), evolve with secondary infection or present a difficult approach.

The current standard treatment is done with pentavalent antimonials. These drugs are parenteral use of exclusive and their use is associated with sometimes severe toxicity, including pancreatitis and cardiac arrhythmias. The restrictions also apply to the use of amphotericin B, a drug of second choice in the treatment of disease that is associated with the occurrence of medication-induced fever and renal dysfunction. Amphotericin B requires hospitalization with elevation in the final cost of treatment.

The miltefosine was safe and effective in treating patients with LC (and LV). Its main adverse effects are related to the gastrointestinal tract, the liver and renal function and rarely dose-limiting. The medication has the added advantage of oral administration.

Preclinical studies indicated a teratogenic potential of Miltefosine, but no clinical experience is available on the use of this medicine during pregnancy in humans. Therefore, pregnancy should be strictly avoided during this study and in a period of 2 months after treatment ends. Preclinical studies in rats showed a dose effect and time-dependent in male fertility, no corresponding toxicity was observed in dogs. The after-treatment of Indian patients males during the reproductive performance and semen analysis before and after the use of Miltefosine (Colombia) as well as after treatment only (in India) did not suggest an adverse effect of Miltefosine on the male fertility.

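### Required adverse-event recording ends with study treatment, while enquiry, safety tests and the pregnancy precaution continue, so the safety endpoint can miss late events

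*Protocol*

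**What the plan says.** - Section 2 names "Incidence and severity of adverse events" as a secondary endpoint and gives no period over which it is counted.
- Section 3.4, under the procedures for adverse events, sets the duty to record: "All adverse events that occur during the study treatment should be documented, regardless of the assumption of a causal relationship". Just before this it says "The investigator should ask the patient at each visit" about medical problems, with no time limit.
- Section 3.3.3 says of miltefosine: "The duration of study treatment is 28 days". Section 4.3 says: "The end of treatment will be the 28th day in the case of regular treatment". For a patient who stops early, the end-of-treatment assessments move to the time of stopping.
- Section 4.2 lists adverse events as "continuously", beside items on days 7, 14 and 21. Section 4.3 lists them once more. Section 4.4 ("Assessments 2 weeks, 1 month and 2 months after the end of the treatment") has efficacy variables only. Section 4.5 adds vital parameters and laboratory tests at 6 months, but not adverse events.
- Section 5.2 says "pregnancy should be strictly avoided during this study and in a period of 2 months after treatment ends".
- Section 3.4, on routine safety parameters, requires an abnormality of major relevance to be entered on the adverse event form as well. Relevance means that it is a serious adverse event, led to premature discontinuation, or needed a therapeutic measure. No time limit is given.

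**The concern.** The recording rule and the visit lists agree that the duty to document general adverse events ends with treatment. The rest of the protocol assumes that safety is still being observed: patients are questioned, blood is drawn, vital signs are taken and a reproductive risk is acknowledged. What those contacts reveal has, for the most part, no required place in the data.

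Safety is part of the trial objective, and adverse-event incidence is the endpoint that serves it. The gap lies in collection, so a statistical analysis plan cannot repair it: an event that was never recorded cannot be analysed. The trial is also open label, so where recording is optional, what gets written down may depend on knowledge of the treatment.

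**Working it through.** The protocol gives no figure to reproduce. The check is mainly a comparison of its sections.

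**1. Visits after treatment.** Five of the 11 flowchart visits (7 to 11) fall after treatment.

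| Visit | Adverse events listed in Section 4 text? | Safety measurements scheduled |
|---|---|---|
| 7 (2 weeks) | No (4.4) | None |
| 8 (1 month) | No (4.4) | Blood count, biochemistry, urine, vital signs (flowchart) |
| 9 (2 months) | No (4.4) | Vital signs (flowchart) |
| 10 (4 months) | No (visit appears only in the flowchart) | Vital signs (flowchart) |
| 11 (6 months) | No (4.5) | Vital signs (4.5 and flowchart); laboratory tests (4.5 only) |

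Four of the five visits take a safety measurement and none lists adverse events. The 6-month laboratory tests in Section 4.5 are absent from the flowchart, and the 1-month tests in the flowchart are absent from Section 4.4. These entries also need reconciling.

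**2. Share of observation covered.** Treatment lasts 28 days. Six months of follow-up is taken as 180 to 183 days.

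- 28 / (28 + 180) = 13.5%
- 28 / (28 + 183) = 13.3%

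This is 28 of about 210 days, or 13%. It is a share of calendar time, not of risk.

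**3. What must be recorded after treatment.**

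- Laboratory, vital-sign or ECG abnormality of major relevance: yes, on a reasonable reading of the routine-parameter rule.
- Lesser laboratory abnormality: classified by the investigator, but not required on the adverse event form.
- Symptom reported at a visit: asked about, no duty to record.
- Serious event without a routine-parameter finding: no duty. No section gives serious events a period of their own.
- Pregnancy within the 2-month period: no duty. No pregnancy test is scheduled after the end of treatment, although congenital anomaly is part of the serious-event definition.

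**4. Equal time.** The window ends when treatment ends. Section 3.3.3 has patients who do not tolerate miltefosine leave treatment, with no dose reduction planned. As an illustration, a patient who stops on day 14 has 14/28 = half the required window of one who completes. Section 3.3.3 gives no duration for antimony. Section 4.3 sets day 28 without naming an arm, so equal windows are not clearly fixed.

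**5. Could late events occur at all?** This needs an assumed late-event rate p per patient, which the protocol does not give. The chance of at least one event among n patients is 1 − (1 − p)^n, with n = 60 for miltefosine and n = 30 for control (Section 3.2).

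| Assumed p | n = 60 | n = 30 |
|---|---|---|
| 1% | 1 − 0.99^60 = 45% | 1 − 0.99^30 = 26% |
| 5% | 1 − 0.95^60 = 95% | 1 − 0.95^30 = 79% |
| 10% | 1 − 0.90^60 = 99.8% | 1 − 0.90^30 = 96% |

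The arms differ here only because their sizes differ. The table says nothing about bias between them.

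**The case against.** The strongest reply is that the text does not shut out late events altogether. The routine-parameter rule in Section 3.4 has no time limit and defines relevance, so a clinically important laboratory finding at the 1-month visit has a mandatory route onto the adverse event form. This stands. A reader might infer that all toxicity first seen at that visit is lost, and the protocol does not support that inference.

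Enquiry at each visit and the continuous listing in Section 4.2 can also be read as implying later collection. This stands in part, because it makes the text contradictory. But asking is not recording, and the continuous entry sits in the on-treatment list, with adverse events listed separately at the end of treatment and nowhere later.

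Three further limits stand:

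- The flowchart has no adverse-event row for any visit, on treatment or after, so its silence about later visits proves nothing.
- No passage says that the endpoint counts only what the recording rule requires. The analysis window may be set in a plan that is not shown. The defect is in what must be collected.
- The contraception criterion in Section 3.2.2 and the end-of-treatment pregnancy test in Section 4.3 address the reproductive risk. They do not provide for recording a pregnancy that occurs afterwards.

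**Conclusion.** The point holds as a gap and a conflict in required collection. If the protocol is followed to the letter, late symptoms, serious events without a routine-parameter finding, lesser abnormalities and pregnancies need not be recorded, and adverse-event incidence is not collected over equal time for all patients. The required window is about 13% of observation, taking 28 days of treatment and 6 months of follow-up.

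A reader might go further and infer that the comparison between arms is biased, or that a known number of events will be missed. Neither is supported. The protocol gives no late-event rate, 5% is only an assumption, and nothing shows that unrecorded events would favour one arm. The change should be made because uncollected data cannot be recovered and the visits already exist.

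**What to change.** - In Section 3.4, replace the limit to study treatment with a window from first dose to one fixed study day. It should be the same in both arms, kept for patients who stop early, and not earlier than the 2-month post-treatment visit.
- Record serious adverse events and pregnancies to the 6-month visit. A term birth would usually fall after that visit, so the sponsor should also state whether the outcome of a recorded pregnancy is followed.
- Add adverse events to Sections 4.4 and 4.5, and add an adverse-event row to the flowchart for every visit.
- State the same window in the endpoint definition in Section 2.
- Record the start date of rescue treatment and report events after it separately. Sections 3.3.3 and 3.4 provide for rescue with antimony after treatment failure. Without this separation, a longer window would count toxicity of rescue antimony against miltefosine.

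The cost is some extra case report form pages at visits that already take place, and a slightly higher reported incidence. No treatment rule changes.
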